### Power calculation

Power calculations were based on BMI, our primary outcome. We aimed to detect a clinically important difference of at least 0.5 kg/m^2^ between intervention and control groups, and assumed a standard deviation of 3.0 kg/m^2^. To calculate the design effect due to the cluster design of the study, we estimated the average number of participants at each school would be 150, and, based on previous research [17], that the ICC = 0.005; thus the design effect was 1.75. Consequently, we calculated that if 1200 students from 8 schools completed the study we would have 80% power to find a clinically important difference in BMI between the intervention and control groups, with α = 0.05 (one-sided).

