## Background

Childhood obesity has become a global epidemic [1]. China is one of many countries to be dramatically affected by this growing epidemic in recent years [2,3]. Obesity has many serious health and financial consequences [4-6]. Excess body weight during adolescence not only predicts adult obesity but also influences morbidity and mortality in adult life [7]. Treating obesity is both difficult and costly [8]. The obesity epidemic demands urgent population-based research on childhood obesity prevention programs to determine which programmes are effective and sustainable.

Schools are critical settings for promoting lifelong healthy eating and physical activity (HEPA) [9,10], and for preventing childhood obesity [10,11]. Several systematic reviews [12-15] and some recent studies [16-19] have shown that school-based prevention of obesity is feasible and effective; however other studies have not shown significant effects [20-22]. Although these school-based intervention studies have generally focused on improving healthy eating behavior and the promotion of physical activity (PA), different strategic components and follow-up periods make it difficult to compare the study results. Moreover, most of these studies were conducted in Western countries, and results from Western countries may not be directly applicable to the Chinese population, given obvious differences in school activities and structures between Western and Chinese societies (e.g., Chinese school students spend much more time in academic study) [23]. Hence, there is a need for a well-designed school-based intervention programme for obesity prevention in Chinese population.

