### Statistical analysis

Descriptive statistics were calculated. Between group difference was examined for treatment assignment and overweight status. Differences were tested using independent t-tests for continuous variables (eg, BMI) and chi-square tests for categorical variables (eg, overweight, lifestyle factors and obesity related knowledge). Multilevel regression models will be used to test for post-test group differences on the main outcome variables corrected for pre-test measurements. Data will be double entered and cleaned with EpiData 3.0 (The Epidata Association, Odense, Denmark), and managed and analyzed using SPSS 13.0 (SPSS, Chicago, Illinois). P < 0.05 is used to assess statistical significance.

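### The stated 80% power does not follow from the power section's own inputs, which give about 70% one-sided

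*Protocol article*

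**What the plan says.** The Power calculation section of the protocol article sets out a complete calculation. The outcome is fixed: "Power calculations were based on BMI, our primary outcome". The target is fixed: "We aimed to detect a clinically important difference of at least 0.5" kg/m². The section "assumed a standard deviation of 3.0" kg/m². On clustering, "we estimated the average number of participants at each school would be 150", the ICC is 0.005 and the design effect is given as 1.75. The significance level is 0.05, one-sided. From these inputs the section concludes that "if 1200 students from 8 schools completed the study we would have 80% power", and it presents that conclusion as their consequence.

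Two other places bear on the point. Study design and recruitment of participants fixes 8 schools, four per group. Statistical analysis plans multilevel regression of the post-test outcome, "corrected for pre-test measurements", and judges significance at P < 0.05 without naming a side. Neither section gives a correlation between baseline and follow-up BMI.

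**The concern.** Every quantity needed to check the 80% is printed beside it, so the figure should reproduce to within rounding. It is nearly ten percentage points too high. It is the only power figure the article gives for the primary outcome, and readers will use it to interpret the BMI result. If the trial finds no significant difference, they will take it that a true effect of 0.5 kg/m² had an 80% chance of being detected. The printed calculation does not support that.

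**Working it through.** **Inputs** (Power calculation section unless noted): difference d = 0.5; SD s = 3.0; pupils per school m = 150; ICC = 0.005; one-sided alpha 0.05; 1200 completers in 8 schools. The allocation of four schools per group comes from Study design and recruitment of participants, so n = 600 per arm.

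**1. Design effect.** 1 + (m − 1) × ICC = 1 + 149 × 0.005 = 1.745, which rounds to the stated 1.75. This reproduces.

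**2. Power on the stated inputs, normal approximation.**
- SE = s × √(2 × DE / n) = 3 × √(2 × 1.75 / 600) = 0.2291
- d / SE = 0.5 / 0.2291 = 2.182
- One-sided: Φ(2.182 − 1.645) = Φ(0.537) = 70.4% (70.6% with DE = 1.745)
- Two-sided: Φ(2.182 − 1.960) = Φ(0.222) = 58.8% (58.9% with DE = 1.745)

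The stated figure is 80%. It does not reproduce.

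**3. Small number of clusters.** Eight schools in two arms leave 8 − 2 = 6 degrees of freedom for the between-school comparison. A noncentral t with 6 df and noncentrality 2.182 gives 61% one-sided (critical value 1.943) and 45% two-sided (critical value 2.447).

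**4. Detectable difference at 80% power, normal approximation.**
- One-sided: (1.645 + 0.842) × 0.2291 = 0.57 kg/m²
- Two-sided: (1.960 + 0.842) × 0.2291 = 0.64 kg/m²

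**5. Could another standard calculation explain the 80%?**

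| Variant | One-sided | Two-sided |
|---|---|---|
| As stated (DE 1.75) | 70.4% | 58.8% |
| No design effect | 89.3% | 82.3% |
| 1200 per arm | 92.5% | 87.0% |
| n divided by √1.75 | 80.6% | 70.9% |
| Alpha 0.10 | 81.6% | – |

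The two one-sided variants that land near 80% both contradict what is printed: one misapplies the design effect, the other changes alpha.

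**6. The planned baseline-adjusted model.** With pre/post correlation r (an assumption; the article gives none) and the same design effect, the SD becomes s × √(1 − r²), so d / SE = 2.182 / √(1 − r²).

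| r | d / SE | One-sided, normal | One-sided, 6 df |
|---|---|---|---|
| 0 | 2.182 | 70% | 61% |
| 0.48 | 2.487 | 80% | 71% |
| 0.5 | 2.520 | 81% | 72% |
| 0.7 | 3.056 | 92% | 85% |
| 0.8 | 3.637 | 98% | 94% |

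On the normal approximation, 80% is reached at r of about 0.48.

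**7. Pupils needed for an unadjusted 80% with 8 schools.** Before clustering, the need is 2 × (1.645 + 0.842)² × 9 / 0.25 ≈ 446 per arm, rounded up. With four schools per arm, 4m / [1 + (m − 1) × 0.005] = 446, which gives m ≈ 251 per school, or about 2000 pupils in total. The design effect grows with m, so multiplying by a fixed 1.75 understates the need.

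**The case against.** The strongest reply is that the trial's test is not the unadjusted comparison. The Statistical analysis section plans a model corrected for the pre-test value, and step 6 shows that a moderate baseline correlation brings power to 80% or above on the normal approximation. This stands as a limit on the finding. A reader might infer from the 70% that the trial is underpowered for its planned analysis, and the article does not support that. The reply does not rescue the sentence, however. The power section mentions no correlation or variance reduction and derives the 80% from an SD of 3.0. Nor can one say that 80% fits no analysis at all, since it fits the adjusted one at r of about 0.48. The article simply does not state that assumption.

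Four further criticisms are tempting, and the article does not bear them out:

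- **Attrition.** The power sentence is conditional on completers, and nothing says that 150 per school is the recruited number, so an assumption of no loss is only an inference.
- **Source of the ICC.** Borrowing it from previous research is disclosed and ordinary. The Background's caution about Western studies does not mention ICCs.
- **Unadjusted SD.** Using it when the model adjusts for baseline is conservative, not wrong.
- **A required total of about 1,558.** One might get this from 445 × 1.75 × 2, but it holds 150 pupils per school and so implies more than 8 schools. With 8 schools it means about 195 per school, a design effect of 1.97 and only about 76% power.

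It can also be said that the intervention and the first follow-up are past, so a corrected figure changes no estimate or test. That is true. It limits the consequence to how the result is interpreted.

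**Conclusion.** The stated 80% is wrong on its own inputs. The correct figure is about 70% one-sided by normal approximation, and about 61% once the 6 between-school degrees of freedom are recognised. If the P < 0.05 rule were applied two-sided, which the article does not specify, the figures would be 59% and 45%. At 80% power the detectable difference is about 0.57 kg/m² (one-sided, normal approximation), not 0.5.

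These results rest only on printed inputs and equal arms of 600. The conclusion concerns the stated calculation. Whether the planned adjusted analysis has 80% power depends on a correlation the article does not give: about 0.48 suffices on the normal approximation with an unchanged design effect, but the same value gives only about 71% on 6 df.

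**What to change.** Correct the last sentence of the Power calculation section in one of two ways.

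- **Keep the unadjusted calculation.** State that 1200 completers in 8 schools give about 70% one-sided power for 0.5 kg/m² by normal approximation, and note that this is about 61% when the 8 clusters are allowed for. Or state that the difference detectable with 80% power is about 0.57 kg/m² (one-sided, normal approximation).
- **Match the planned model.** State the pre/post BMI correlation assumed, give its source, and report the power that follows, saying whether it uses the normal approximation or 6 degrees of freedom.

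The cost is one recalculation and a reworded sentence. On the first route the published figure becomes less favourable. Neither route changes enrolment, the number of schools or the analysis.

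### Power is planned at one-sided alpha 0.05 while the analysis threshold of P < 0.05 has no stated direction, and the stated 80% power holds under neither reading

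*Protocol article*

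**What the plan says.** The Power calculation section of the protocol article names BMI as the outcome that drives the sample size: "Power calculations were based on BMI, our primary outcome". The target is a "difference of at least 0.5 kg/m^2^ between intervention and control groups", and the authors "assumed a standard deviation of 3.0 kg/m^2" (squared metres). For clustering, "we estimated the average number of participants at each school would be 150", and previous research is cited for the assumption "that the ICC = 0.005; thus the design effect was 1.75". With 1200 students from 8 schools completing, the section claims 80% power "with α = 0.05 (one-sided"). It gives no reason for choosing a one-sided test.

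The Statistical analysis section names t-tests for continuous variables, chi-square tests for categorical variables, and multilevel models for post-intervention group differences on the main outcomes, corrected for the baseline measurement. It gives one decision rule for all of them: "P < 0.05 is used to assess statistical significance". No direction is attached to that rule or to any named test.

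**The concern.** The article itself fixes both the planning alpha and the decision threshold, yet a reader cannot tell whether they describe the same test.

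- If P < 0.05 is two-sided, the sample size was calculated for a test that will not be run.
- If it is one-sided, the chance of falsely declaring a benefit is 5%, against 2.5% under a two-sided 5% test, and a higher BMI in the intervention schools could not be declared significant.

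The practical risk is a favourable result with two-sided P between 0.05 and 0.10. It is positive under the planning alpha and negative under the ordinary reading of the analysis section. According to the Study design section, the first follow-up survey (May 2011) had already been carried out when the article was written, so the choice should not stay open until results are seen.

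The power statement is also a figure that readers will use to judge a null result, so it should be correct for whichever test is meant.

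**Working it through.** **Inputs, all from the protocol article.** Difference 0.5 kg/m², SD 3.0 kg/m², 150 students per school, ICC 0.005, stated design effect (DE) 1.75, 1200 completers (Power calculation); four schools per arm (Study design), hence 600 students per arm, assuming equal school sizes. No further dropout allowance is needed, because 1200 counts completers.

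**Design effect.** 1 + (150 − 1) × 0.005 = 1.745, which the article rounds to 1.75. This reproduces.

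**Standard error (normal approximation, no baseline adjustment).**
- Effective n per arm = 600 / 1.75 = 342.9
- SE = 3.0 × √(2 / 342.9) = 0.229 kg/m²
- Standardised effect = 0.5 / 0.229 = 2.182

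**The plan's own figure: 80%, one-sided 0.05.**
- Power = Φ(2.182 − 1.645) = 70.4% (70.6% with DE 1.745)
- The stated 80% does not reproduce.

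**The same inputs, two-sided 0.05.**
- Power = Φ(2.182 − 1.960) = 58.8% (58.9% with DE 1.745)

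**Other ways the 80% might have arisen.**

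| Variant | One-sided | Two-sided |
|---|---|---|
| Normal approximation, DE 1.75 | 70.4% | 58.8% |
| t-test, individual-level df | 70.4% | 58.7% |
| t-test, 6 cluster-level df | 61.2% | 45.0% |
| No design effect | 89.3% | 82.3% |
| 1200 read as per arm | 92.5% | 87.0% |

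None lies within 2 points of 80%. The nearest, two-sided with no design effect, contradicts the stated inputs twice.

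**Splitting the gap.** 80 − 70.4 = 9.6 points are lost before sidedness enters. 70.4 − 58.8 = 11.6 points come from moving from one-sided to two-sided.

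**Detectable difference at 80% power.**
- One-sided: (1.645 + 0.842) × 0.229 = 0.57 kg/m²
- Two-sided: (1.960 + 0.842) × 0.229 = 0.64 kg/m²

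Both exceed the 0.5 kg/m² that the article calls clinically important.

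**Completers for 80% power, to show scale only.** Per arm 2 × (sum of z)² × 3.0² / 0.5², rounded up, then × 1.75 × 2:
- One-sided: 446 × 1.75 × 2 = 1561
- Two-sided: 566 × 1.75 × 2 = 1981

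**Size of the ambiguous zone.** With SE 0.229, two-sided P between 0.05 and 0.10 corresponds to an estimated BMI benefit between 1.645 × 0.229 = 0.38 and 1.960 × 0.229 = 0.45 kg/m².

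**Baseline adjustment.** The planned multilevel model corrects for baseline, but the article gives no baseline correlation r and the power calculation takes no credit for it. As an assumption, let adjustment multiply the variance by (1 − r²) and leave the design effect unchanged. Two-sided power is then Φ(2.182 / √(1 − r²) − 1.960):
- r = 0.5: Φ(2.520 − 1.960) = 71%
- r = 0.7: Φ(3.056 − 1.960) = 86%
- r = 0.8: Φ(3.637 − 1.960) = 95%

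**The case against.** The strongest reply is that the two sections do not contradict each other. Both use 0.05, and a t-test or a regression coefficient can be tested one-sided. A condensed article may leave the direction of each test to the full analysis plan. This stands in part. A reader might infer that the analysis is committed to non-directional tests, and so to a different error rate from planning, but the Statistical analysis section never says so for the BMI t-test or the multilevel model. The chi-square tests do not settle it: they concern categorical variables such as overweight, lifestyle and knowledge, not mean BMI. What remains is that one section fixes a direction and the other omits it, and that an unqualified P < 0.05 for group differences is ordinarily read as two-sided.

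A second reply is that 59% is not the power of the planned analysis, because the model adjusts for baseline BMI. That is fair, and the adjusted power could well be higher. But the article's calculation does not use the adjustment, so it cannot rescue the stated 80% as written. With only eight schools, a test on 6 degrees of freedom would pull the unadjusted figure the other way, to 45% two-sided.

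A third reply is that a favourable direction was a reasonable expectation. The Background reports that other school studies found no significant effect, which is not evidence of harm, and that several reviews found such programmes effective. So the documents do not show that a one-sided test is indefensible; they show that none is defended.

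**Conclusion.** The point holds in two parts.

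First, sidedness is fixed as one-sided for planning, without a reason, and left unstated for analysis. The documents support an ambiguity to be reconciled, not a proven mismatch of error rates.

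Second, the stated 80% power is wrong under either reading: about 70% one-sided and about 59% two-sided on the article's own inputs. A reader who sets 59% beside 80% might infer that sidedness explains the whole 21-point shortfall. It does not. About 10 points are an error inside the one-sided calculation and about 12 are the cost of a two-sided test, so settling the sidedness alone would not restore the stated power.

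These figures assume equal arms of 600 completers, the normal approximation, the stated design effect and no baseline adjustment. The first part rests on the wording alone and does not depend on these assumptions.

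**What to change.** 1. State one sidedness in both the Power calculation and the Statistical analysis sections before the outcome analysis. Two-sided 0.05 with 95% confidence intervals is preferable, since it matches the ordinary reading of the existing threshold. If one-sided testing is kept, say so in both places and justify it.
2. Replace the 80% with the power, or the detectable difference, for the test that will be run. Two-sided and unadjusted, that is about 59%, or 0.64 kg/m² at 80% power.
3. If credit is taken for the baseline adjustment, give the assumed baseline correlation with its source and show a range, for example about 71% at r = 0.5 and 86% at r = 0.7 (two-sided, design effect unchanged).

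The cost is wording, one recalculation and a stated power that looks less favourable unless a baseline correlation can be supported. No increase in enrolment is proposed.

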### Statistical analysis

Descriptive statistics were calculated. Between group difference was examined for treatment assignment and overweight status. Differences were tested using independent t-tests for continuous variables (eg, BMI) and chi-square tests for categorical variables (eg, overweight, lifestyle factors and obesity related knowledge). Multilevel regression models will be used to test for post-test group differences on the main outcome variables corrected for pre-test measurements. Data will be double entered and cleaned with EpiData 3.0 (The Epidata Association, Odense, Denmark), and managed and analyzed using SPSS 13.0 (SPSS, Chicago, Illinois). P < 0.05 is used to assess statistical significance.

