**Methods/design:**

We designed a cluster randomized controlled trial in 8 randomly selected urban primary schools between May 2010 and December 2013. Each school was randomly assigned to either the intervention or control group (four schools in each group). Participants were the 4^th^ graders in each participating school. The multi-component program was implemented within the intervention group, while students in the control group followed their usual health and physical education curriculum with no additional intervention program. The intervention consisted of four components: a) classroom curriculum, (including physical education and healthy diet education), b) school environment support, c) family involvement, and d) fun programs/events. The primary study outcome was body composition, and secondary outcomes were behaviour and behavioural determinants.

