(2) Study variables collected in the questionnaire survey

(a) Socio-demographic characteristics: These included student’s age, gender, grade, school, ethnicity, parental educational attainment (classified into 3 subgroups: ≤9 yrs, >9 but ≤ 12 yrs, and ≥13 yrs), and family size and structure.

(b) Obesity-related knowledge: A series of questions were asked regarding knowledge about obesity and its related behavioral risk factors and long-term influence of childhood obesity. All these variables were categorized as “Yes” or “No or do not know”. For example, the question about information on screen time use was “Do you think spending prolonged time in viewing TV or using the computer can result in excess body weight?”

(c) Dietary intake: Items from a specifically validated Frequency Food Questionnaire (FFQ) were selected to gather information on dietary consumption including meat, vegetable/fruit, snack and soft-drinks [32]. All variables will be categorized into tertiles for our analysis.

(d) Physical activity and sedentary behavior: These were assessed using the Chinese version of the International Physical Activity Questionnaire (CHN-IPAQ) [33]. We will calculate moderate physical activity (MPA) time based on time spent in jogging and doubled the time in ball playing and swimming. Time spent on homework, sleep and commuting to/from school were also collected.

(e) Behavior change: Students were asked questions on changes in lifestyle and behavior (dietary intake, physical activity and sedentary behavior) at first follow-up compared to the baseline survey. Responses were recorded on a 5-point Likert scale (increasing a lot, increasing a little, no change, decreasing a little, and decreasing a lot).

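### Pupil-level t-tests and chi-square tests are named for comparing arms although schools were randomised, and a clustered analysis of the secondary lifestyle and knowledge outcomes is not clearly planned

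*Protocol article*

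**What the plan says.** The Abstract (Methods/design) fixes the unit of randomisation: "Each school was randomly assigned to either the intervention or control group (four schools in each group". It also ranks the outcomes: "The primary study outcome was body composition, and secondary outcomes were behaviour and behavioural determinants". The Power calculation section recognises that pupils in one school are correlated. It begins "To calculate the design effect due to the cluster design of the study" and arrives at 1.75 from 150 pupils per school and an ICC of 0.005 for BMI.

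The Statistical analysis section then gives three statements in sequence:

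- The groupings: "Between group difference was examined for treatment assignment and overweight status".
- The tests: "Differences were tested using independent t-tests for continuous variables (eg, BMI"), followed by "chi-square tests for categorical variables (eg, overweight, lifestyle factors and obesity related knowledge"). No time point and no cluster correction is given for either.
- The model: "Multilevel regression models will be used to test for post-test group differences on the main outcome variables corrected for pre-test measurements". The article does not say which variables count as main outcomes.

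The section on data collection shows what form the secondary outcomes take. On the knowledge items it says "All these variables were categorized as “Yes” or “No or do not know". The dietary variables are to be cut into tertiles. The behaviour-change items are 5-point ratings of change since baseline, asked at the first follow-up.

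**The concern.** The independent t-test and the ordinary chi-square test both assume that pupils are independent. In a school-randomised trial they are not, and the plan's own sample size allows for this. A pupil-level test of arm therefore understates the standard error by the square root of the design effect.

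The outcomes exposed are those that the intervention addresses most directly: knowledge, diet and activity. They are classed as secondary, most are categorical, and chi-square is the only test that the text explicitly attaches to them. A false positive there could support a claim that behaviour changed even if BMI did not move. An unadjusted test also ignores the baseline value, although baseline was collected for most of these variables.

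**Working it through.** **Inputs from the documents.** Eight schools, four per arm; m = 150 pupils per school; ICC = 0.005 for BMI; stated design effect 1.75; significance at P < 0.05 with no side stated in the analysis section (the power section uses one-sided 0.05).

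**Step 1. The plan's own figure.** DE = 1 + (m − 1) × ICC = 1 + 149 × 0.005 = 1.745. This agrees with the stated 1.75.

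**Step 2. True error of a pupil-level test at that ICC.** For a t-test or a 2 × 2 chi-square at nominal two-sided 5%, the true error is 2 × [1 − Φ(1.96/√DE)]. Here √1.745 = 1.321 and 1.96/1.321 = 1.484, so the error is 0.138. Confidence intervals are too narrow by the same factor of 1.32. If the test is one-sided at 5%, the error is 1 − Φ(1.645/1.321) = 0.107.

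**Step 3. Tables with more categories.** The error is P(χ² > critical value/DE), assuming that the same design effect applies to every cell.
- Tertiles by arm (2 df): 5.991/1.745 = 3.433, giving about 0.18.
- Five-point scale by arm (4 df): 9.488/1.745 = 5.437, giving about 0.25.

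**Step 4. Range of ICC.** The documents give no ICC for behaviour or knowledge, so these values are assumptions, for a binary outcome with 150 pupils per school:

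| Assumed ICC | DE | True two-sided error |
|---|---|---|
| 0.001 | 1.149 | 0.067 |
| 0.005 | 1.745 | 0.138 |
| 0.01 | 2.49 | 0.214 |
| 0.02 | 3.98 | 0.326 |

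**Step 5. Check by simulation.** Beta-binomial data for 8 schools of 150 pupils with no arm effect were simulated 40,000 times per setting, with prevalences of 20% and 50%. At ICC 0.005 the chi-square test rejected in 14.1% and 14.2% of runs. At ICC 0.02 it rejected in 32.9% and 33.1%. A t-test on the eight school proportions (6 df) stayed between 4.9% and 5.1% at both ICCs.

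**Step 6. Which outcomes have a clustered analysis in the text.**
- BMI: yes. The Power calculation section calls it the primary outcome, so it is a main outcome on any reading.
- Overweight: probably. It is defined from BMI and belongs to body composition, the primary outcome in the Abstract.
- Lifestyle factors and knowledge: unclear. They are secondary in the Abstract and named only with chi-square.
- Behaviour-change items: not as written. They are collected at follow-up as change since baseline, so a model corrected for a pre-test measurement does not fit them, however broadly the main outcomes are read.

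**The case against.** The best defence is that the unadjusted tests are a descriptive step. They follow directly on the descriptive statistics and are in the past tense, whereas the multilevel models are in the future tense, and the multilevel sentence is the only one that mentions differences after the intervention. The same tests also serve comparisons by overweight status, and the text does not say which variables go with which grouping. The term for the main outcomes is plural and is not stated to exclude the secondary ones. Finally, this is a condensed article, and models for secondary outcomes are commonly set out elsewhere.

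Much of this stands. A reader might infer that the trial's effect analysis as a whole ignores clustering; the multilevel sentence rules that out for BMI. A reader might also infer that overweight is left with a chi-square test; as a body-composition measure it more naturally falls under the multilevel models.

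The defence does not remove the point. Tense does not fix the time point, because the Study design section describes the May 2011 survey in the past tense too and only May 2012 as future. The behaviour-change items cannot be a baseline comparison. Even at baseline, pupil-level P values by arm are too small under school randomisation and can suggest imbalance that is not there. And the point concerns a test that the article does name and that conflicts with its design, not a detail that it leaves out.

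**Conclusion.** The point holds in a limited form. The article names tests that ignore school randomisation for comparing arms, does not confine them to description, and leaves unclear whether the secondary lifestyle and knowledge outcomes receive a clustered analysis. For the behaviour-change items, the multilevel model as worded does not fit.

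If these arm comparisons are made at pupil level, P values are too small for any positive ICC. The size is about 13.8% true two-sided error against a nominal 5% if the BMI ICC of 0.005 carries over, and about 7% to 33% over an assumed ICC of 0.001 to 0.02. These figures assume 150 pupils in each school and a two-sided test.

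Two further inferences go beyond the text. One is that the secondary results will certainly be analysed this way. The other is that knowledge and behaviour have a larger ICC than BMI. The second is plausible, since each school's own teachers gave the lessons, but no figure in the article supports it.

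**What to change.** - Use t-tests and chi-square tests for no inferential comparison of arms, and present baseline by arm descriptively.
- Define which variables are the main outcomes.
- State that every primary and secondary outcome is compared between arms with a cluster-adjusted analysis: a school random effect in a model suited to the outcome type (linear, logistic or ordinal), or a comparison of the eight school-level summaries.
- Adjust for the baseline value where one exists. For the behaviour-change items, state the clustered comparison without a pre-test covariate.

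The cost is a few sentences, a little more programming and wider confidence intervals on the secondary outcomes. No change to data collection is needed.
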